# Randomized double-blind placebo-controlled trial of sublingual immunotherapy in children with house dust mite allergy in primary care: study design and recruitment

**DOI:** 10.1186/1471-2296-9-59

**Published:** 2008-10-20

## Abstract

**Background:**

For respiratory allergic disorders in children, sublingual immunotherapy has been developed as an alternative to subcutaneous immunotherapy. Sublingual immunotherapy is more convenient, has a good safety profile and might be an attractive option for use in primary care. A randomized double-blind placebo-controlled study was designed to establish the efficacy of sublingual immunotherapy with house dust mite allergen compared to placebo treatment in 6 to18-year-old children with allergic rhinitis and a proven house dust mite allergy in primary care. Described here are the methodology, recruitment phases, and main characteristics of the recruited children.

**Methods:**

Recruitment took place in September to December of 2005 and 2006. General practitioners (in south-west Netherlands) selected children who had ever been diagnosed with allergic rhinitis. Children and parents could respond to a postal invitation. Children who responded positively were screened by telephone using a nasal symptom score. After this screening, an inclusion visit took place during which a blood sample was taken for the RAST test.

**Results:**

A total of 226 general practitioners invited almost 6000 children: of these, 51% was male and 40% <12 years of age. The target sample size was 256 children; 251 patients were finally included. The most frequent reasons given for not participating were: absence or mildness of symptoms, absence of house dust mite allergy, and being allergic to grass pollen or tree pollen only. Asthma symptoms were reported by 37% of the children. Of the enrolled children, 71% was sensitized to both house dust mite and grass pollen. Roughly similar proportions of children were diagnosed as being sensitized to one, two, three or four common inhalant allergens.

**Conclusion:**

Our study was designed in accordance with recent recommendations for research on establishing the efficacy of sublingual immunotherapy; 98% of the target sample size was achieved. This study is expected to provide useful information on sublingual immunotherapy with house dust mite allergen in primary care. The results on efficacy and safety are expected to be available by 2010.

**Trial registration:**

the trial is registered as ISRCTN91141483 (Dutch Trial Register)

## Background

Specific immunotherapy with allergens might prevent the onset of asthma in individuals with allergic rhinitis and may accelerate the remission of asthma in children with allergic disease. [1-3] Although subcutaneous immunotherapy (SCIT) is an effective treatment of respiratory allergic disorders, [4] the injections can be uncomfortable and side effects, though rare, may be serious and even fatal. [5,6] The use of specific sublingual immunotherapy (SLIT) for treatment of respiratory allergic disorders in children may be a viable alternative to SCIT because of its convenient form of administration and good safety profile – which has allowed home administration of SLIT. [7,8] Thus, although SLIT seems particularly suitable for children in primary care, most clinical trials up to now have been performed in a hospital setting.

Evidence for the efficacy of SLIT in children remains inconclusive. Various reviews concluded that there was insufficient evidence to recommend SLIT for use in routine clinical practice. [9-11] In their Cochrane review, Wilson et al. concluded that SLIT is an accepted treatment for adults; studies with children revealed no significant reduction in symptoms and medication scores, but the number of participants was small. [12]

In 2001, the Allergic Rhinitis and its Impact on Asthma (ARIA) guidelines were published in co-operation with the World Health Organization. [13] They recommend treatment of allergic rhinitis in a stepwise manner (using a combination of allergen avoidance, pharmacotherapy and immunotherapy) based on the duration and severity of disease, rather than on the type of exposure (i.e. seasonal, perennial, occupational) as in previous guidelines. [14] Immunotherapy is recommended for patients with more severe disease, for those not responding to usual treatments, or for those refusing usual treatments; this type of patient is generally treated in a hospital setting and/or by a specialist.

In the Netherlands, allergic rhinitis in children is usually managed by the general practitioner (GP). We hypothesized that SLIT could be an effective treatment in primary care and designed a study to evaluate the efficacy and safety of SLIT in children and adolescents with house dust mite-induced allergic rhinitis. Here we describe the methodology, recruitment, and main characteristics of the primary care study population.

## Methods

### Study design

This ongoing study is a randomized double-blind placebo-controlled study, comparing the efficacy of SLIT with house dust mite allergen (SLIT-HDM) to that of placebo treatment in 6 to 18-year-old children with allergic rhinitis and a proven house dust mite allergy in primary care. Patients entered the study and started treatment either in September-December 2005 or in September-December 2006 for a period of approximately two years. Written informed consent was obtained. The study was approved by the Ethical Review Board of Erasmus MC-University Medical Center Rotterdam. The trial was registered as ISRCTN91141483.

### Participants and recruitment

GPs in south-western Netherlands selected children aged 6 to 18 years in their computerized patient files with either a diagnosis of hay fever/allergic rhinitis or relevant medication use: i.e. antihistamines for systemic use; nasal corticosteroids; topical decongestants; topical anti-allergics, and other nasal preparations.

Recruitment took place September to December in 2005 and in 2006. An information letter signed by the GP was sent to the selected children. This letter described the general purpose of the study, elicited cooperation, and provided a return form and envelope. On the return form children and parents could indicate whether or not they were interested in the study; if not interested they could indicate the reason for not participating.

Participants who responded positively were telephoned by a research assistant to arrange a screening interview (see below). The research assistant asked questions about nasal symptoms during the last three months, the history of allergic rhinitis, general medication use, and use of asthma medication. Table 1 gives an overview of all inclusion and exclusion criteria.

**Table 1 T1:** Inclusion and exclusion criteria for the study population

**Inclusion criteria**
• aged 6–18 years
• history of allergic rhinitis for at least 1 year
• IgE antibodies ≥0.7 kU/l to house dust mite
• no use of nasal steroids in the month before start of baseline measurements
• rhinitis symptom score of at least 4 out of 12 during last 3 months
• signed informed consent
**Exclusion criteria**
• severe asthma (requiring 800 mcg budesonide daily or equivalent for other inhaled steroids; or requiring >3 courses of oral prednisone/prednisolone in previous year or required hospital stay for asthma in previous year)
• sensitization to pets present at home (IgE antibodies ≥0.7 kU/l)
• planned surgery of nasal cavity
• having received immunotherapy in past 3 years
• language barrier
• contraindications to sublingual immunotherapy (as supplied by the manufacturer)

After telephone screening an inclusion visit took place for those who met the inclusion/exclusion criteria and who agreed (children/parents) to further participation. During this visit, the research assistant performed/recorded the following: rhinitis symptoms during the last month and last week (nasal symptoms: rhinorrhea, blocked nose, sneezing, itching); conjunctivitis symptoms during the last month and last week (eye symptoms: tearing, itching, redness); International Study of Asthma and Allergies in Childhood (ISAAC) questionnaire [15] for rhinitis and asthma; wheeze and cough; family history of allergy, asthma and eczema; rhinoconjunctivitis-specific quality of life for pediatrics and adolescents (PRQLQ and AdolRQLQ[16,17]); blood sample for RAST (grass pollen, tree pollen, HDM, cat dander and a pet, if present at home) (CAP-Phadiatop^®^, Pharmacia Diagnostics AB, Uppsala, Sweden); and physical examination (weight and height).

After the screening visit, when children met the inclusion criteria and none of the exclusion criteria and children and parents agreed to participate, a home visit was scheduled to provide instructions about the baseline diary. Every day for one month, children recorded the symptoms related to allergic rhinitis on a diary card; also reported were other complaints, rescue medication, and other medication needed (see below). At this visit the research assistant took dust samples from the child's bedroom floor and mattress to assess indoor HDM exposure. This will be repeated after two years.

After the baseline diaries had been completed a new visit was scheduled and, after signing informed consent, participants were assigned to SLIT treatment or placebo according to the randomization schedule (see below).

### Randomization

Randomization was generated by a computer program in varying block sizes unknown to the investigators. The randomization list was passed to the Department of Pharmacy at Erasmus MC. In order to ensure that disease severity was similar between patients assigned to verum therapy and those assigned to placebo, randomization was stratified according to severity on the basis of data obtained during the telephone screening.

### Intervention

Participants received an aqueous extract of house dust mites (*Dermatophagoides pteronyssinus) *in a glycerinated isotonic phosphate buffered solution (Oralgen Mijten, Artu Biologicals, Lelystad, the Netherlands) or placebo treatment consisting of the glycerol solvent. In accordance with the manufacturer's guidelines the treatment period was divided into two phases: a dose escalation phase of 20 days, and a maintenance phase of approximately two years. Treatment started on day one with a single drop. One drop consisting of 0.05 ml corresponds with 35 biological units (BU); the dose was increased by one drop per day until day 20 (20 drops = 1 ml = 700 BU). The maintenance dose was 20 drops (= 700 BU) twice weekly. The drops were administered sublingually and kept there for at least 1 minute before being swallowed. A research assistant instructed the participants and also provided written instructions. Participants, parents, investigators, research assistants and caregivers were blinded to treatment allocation.

### Follow-up

Figure 1 shows the time schedule per individual patient. After randomization children started with treatment for 20 days (dose escalation phase) followed by a maintenance phase of two years. Children filled in a diary during three months (between September and December) after one and two years of treatment (see below). Every month a research assistant completed a questionnaire (conducted by telephone) throughout the entire study period. Over the two years of treatment the total number of planned contacts is 13 home visits and 23 telephone calls.

**Figure 1 F1:**
[figure not shown]
Detailed time schedule per individual patient.

### Outcome measures

The primary outcome measure for efficacy is the difference between the group receiving SLIT and the group receiving placebo for the total daily mean rhinitis symptom score for four nasal symptoms (see below), assessed through a diary filled in during three months after two years of treatment. In the period of evaluation (September through December), the percentage of days on which the daily symptoms are properly recorded should be at least 50%. For patients who do not meet this criterion in the second year (e.g. dropouts after 1 year) data of the first treatment year will be used. See section Data analysis for further details.

Secondary outcome measures are the difference between the group receiving SLIT and the placebo group for the proportion of symptom-free days, the proportion of rescue medication-free days, use of rescue medication, mean eye symptom score, total symptom score (nasal and eye symptoms), and disease-specific quality of life after two years of treatment. Overall evaluation of the treatment effect will be assessed by patient, parents and research assistant after two years of treatment.

### Assessment of efficacy

Efficacy will be measured by patient-assessed symptom scores. Although nasal, eye, skin and lung-related symptoms have been related to house dust mite allergy, the main allergic symptoms are considered to be the following nasal symptoms: sneezing, itching, watery running nose and blockage. The intensity of these symptoms is subjectively assessed according to a grading scale: 0 = no complaints, 1 = minor complaints, 2 = moderate complaints and 3 = serious complaints; the maximum score is 12. The scores will be assessed daily by the patient and recorded in the patient's diary. The period of measurement will be three months in the period September through December in 2006 and 2007 for the primary outcome measures (first cohort), and in 2007 and 2008 (second cohort); this autumnal period of the year was chosen because it has the highest HDM exposure levels.

### Assessment of safety, tolerability and compliance

Adverse effects will be assessed by patients and parents reporting effects in the diary, or calling the research assistant with complaints, or by the research assistant via a questionnaire filled in during home visits, and by monthly telephone contact. All adverse events reported during the study will be recorded. In case of serious adverse events or persisting allergic symptoms after management according to protocol, the study treatment will be discontinued for these patients. If patients discontinue the study medication, they will be asked to agree to further follow-up according to the study protocol during the remainder of the study period.

Compliance will be measured by self-report of SLIT administration in the diary and by monthly telephone contact, and determined by weighing the returned study medication.

### Sample size calculation

As rhinitis symptoms are the primary outcome measure, this was used for calculating the sample size. A Dutch study on mattress covers provides relevant data for symptom scores in patients with house dust mite allergy (aged 8–50 years). [18] Based on the baseline symptom score in the latter study, and the ability to assess a reduction of at least 30% (proposed by Malling as a clinically relevant reduction) [19], in our study a sample size of 96 patients per group would be required. Taking into account a dropout rate of 25% between randomisation and end of follow-up, this would require 128 patients in each study group. An alternative approach is assuming the nasal score at the last week screening visit to be 4.5 (sd 2.6). A 30% change would provide a delta of approximately 0.5 (generally assumed to be clinically relevant) and require a sample size of 105 per study group (alpha = 0.05 and beta = 95%).

### Quality of life

Rhinoconjunctivitis-specific quality of life will be assessed through the validated Pediatric (6–11 years) and Adolescent (12–17 years) Rhinoconjunctivitis Quality of Life Questionnaire (PRQLQ and AdolRQLQ, respectively) at baseline and after one and two years. [16,17] To establish the presence of lower airway symptoms during the last 12 months at baseline, specific questions on wheezing and dry cough at night were taken from the ISAAC. [15]

### Rescue medication

During the study the use of symptomatic allergy medication is discouraged, especially use of long-acting antihistamines and locally or generally administered corticosteroids. However, rescue treatment is allowed in case of persisting allergic symptoms (levocetirizine tablets, xylomethazoline nasal spray and levocabastine eye drops); the above-mentioned rescue medication will be provided free of charge. In principle, patients are encouraged to use the provided medication only, but are allowed to use their own medication as well. Patients were clearly instructed on the use of rescue medication and other medication, and on how to document entries in the patient diary. For severe or steadily worsening rhinoconjunctivitis symptoms or intermittent asthma the patient should consult his/her physician.

### Data analysis

The treatment effect will be tested at a two-sided significance level of 5%. Statistical comparison between verum and placebo of the mean daily sum score from the diary after two years will be done using Analysis of Covariance. There will be three covariates in this analysis: baseline nasal sum score at entry into study, age of patients, and presence of cat allergy. In case more than one child from the same family has been included in the study and contribute to the final analysis, we will test whether 'family' provides a statistically significant effect (P < 0.20). In that case 'family' will be added as a random effect.

Exploratory subgroup analyses are planned for the difference between placebo and verum regarding the primary outcome according to age and the baseline symptom score (both dichotomized at the median value).

All analyses will be performed according to the intention-to-treat principle, i.e. irrespective of compliance with the prescribed dosing schedule and other treatments, but excluding patients in whom major inclusion criteria were not fulfilled. A per-protocol analysis will include all patients who took at least 80% of the study medication and completed 50% of the diaries.

For this paper, the distribution of age and gender throughout the recruitment period will be compared. All data are presented as summary descriptive statistics: means, standard deviations (SD) or percentages. Statistical analyses were carried out with SPSS version 11.0 and differences of p < 0.05 were considered significant.

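### The primary ANCOVA omits the severity stratum used at randomisation, and the text does not say which baseline score might stand in for it

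*Protocol article*

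**What the plan says.** The Randomization section gives the method, "Randomization was generated by a computer program in varying block sizes unknown to the investigators", and the one stratification factor: "randomization was stratified according to severity on the basis of data obtained during the telephone screening". The stated purpose is balance on severity between the arms. No other factor is named, and neither the cut-point nor the number of strata is given.

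The Data analysis section defines the primary model: "Statistical comparison between verum and placebo of the mean daily sum score from the diary after two years will be done using Analysis of Covariance". It then lists the adjustment terms: "There will be three covariates in this analysis: baseline nasal sum score at entry into study, age of patients, and presence of cat allergy". The only other term it allows is a random family effect, to be added if siblings are enrolled and the effect passes a P < 0.20 screen.

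On timing, the Study design section describes two intakes, "Patients entered the study and started treatment either in September-December 2005 or in September-December 2006". Under Assessment of efficacy, the diary autumns are given as "2006 and 2007 for the primary outcome measures (first cohort), and in 2007 and 2008 (second cohort").

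**The concern.** When allocation is forced to balance on a factor that predicts outcome, the treatment estimate varies less from one randomisation to the next than under simple randomisation. A model that leaves the factor out keeps its contribution in the residual variance. The reported standard error is then larger than the real one: the interval is too wide, the test is conservative and some precision is lost. The usual remedy is to analyse by the strata used to randomise.

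This is not a detail that the article leaves to a fuller plan. It states the number of covariates and names each one, and the stratum is not among them. The baseline nasal score is itself a measure of severity and could absorb much or all of the stratum's effect, but that depends on which measurement it is, and the article does not say.

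**Working it through.** **1. Candidates for the baseline score.** The article records at least four nasal measurements before treatment:
- telephone screening, mean 6.8 (SD 2.1) (Table 3)
- screening visit, last three months, 5.8 (SD 2.3) (Table 3)
- screening visit, last week, 4.5 (SD 2.6) (Table 3)
- the one-month baseline diary completed before assignment (Participants and recruitment)

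Any of these could be the score at entry. If it is the telephone measure used for stratification, most of the problem disappears. If it is a visit or diary score, the stratum is represented only through its correlation with that score.

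**2. The plan's own figures.** Neither depends on the covariates.
- Alternative sample size: n per group = 2(z₀.₉₇₅ + z₀.₉₅)²/d² = 2(1.960 + 1.645)²/0.5² = 104, against 105 stated. This reads the printed beta of 95% as power.
- Dropout: 96/(1 − 0.25) = 128, as stated.

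The first is an unadjusted two-mean calculation, so adding a stratum term does not alter it. The 96 cannot be re-derived, because the mean and SD of the mattress-cover study are not given.

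**3. Simple bound on the standard error.** Let r be the partial correlation of the stratum with the two-year score, given the other covariates. The documents give no value, so a range of 0 to 0.3 is assumed. The share of residual variance left in is r², and the overstatement of the SE is 1/√(1 − r²).

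| r (assumed) | r² | SE ratio |
|---|---|---|
| 0 | 0 | 1.000 |
| 0.1 | 0.01 | 1.005 |
| 0.3 | 0.09 | 1.048 |

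**4. Simulation.** Assumed inputs:
- 192 evaluable patients (2 × 96)
- two severity strata, permuted blocks of 2, 4 and 6
- correlation of telephone severity with the baseline covariate of 0.3, 0.5 or 0.7
- standardised baseline coefficient 0.5
- extra effect of telephone severity, given baseline, of 0 to 0.3 SD
- 5000 runs per setting; age and cat allergy left out for simplicity

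| Model | Model SE / true SD of estimate | Type I error |
|---|---|---|
| Baseline score, no stratum | 0.99 to 1.05 | 3.8% to 5.2% |
| Baseline score plus stratum | 0.985 to 1.02 | 4.1% to 5.3% |
| No covariates (not this plan) | 1.01 to 1.19 | 2.0% to 5.0% |

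Monte Carlo error is about 0.3 percentage points on the type I error and about 1/√(2 × 5000) = 1% on each SE ratio, so ratios just below 1 are noise. Comparing the two models on the same runs, the stratum lowers the mean SE by 0 to about 4%. The largest fall is from 0.1167 to 0.1121, and 0.1121/0.1167 = 0.961.

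**5. Power.** The planned effect is 0.3 × 4.5/2.6 = 0.519 SD. In the setting with the largest gain, power moves from 99.4% to 99.6%; in every setting the change is under half a point. Power is near its ceiling there, so this understates the gain for a smaller true effect. With that same gain, a comparison with 80% power (effect/SE = 2.80) would have 2.80 × 0.1167/0.1121 = 2.92, and Φ(2.92 − 1.96) = 83%. That is the best case under these assumptions, not the expected one.

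**The case against.** The strongest defence is that the plan already adjusts for baseline nasal severity, so little is left for the stratum to explain. That largely stands. The marked conservatism in the simulation (SE up to 19% too large) occurs only with no covariates, which is not what is planned. If telephone severity adds nothing beyond the baseline score, the planned standard error is right.

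A reader might infer four stronger things that the article does not support.

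- **That the baseline score fails to represent the stratum because the means differ (6.8, 5.8, 4.5).** A difference in means says nothing about correlation, and ANCOVA is unaffected by a constant shift in a covariate. Lower later means are also expected after selection on a telephone score of at least 4, and with different recall windows.
- **That the 0–12 telephone score is the stratifier.** The Randomization section speaks only of severity based on telephone data. That call also covered rhinitis history, general medication and asthma medication.
- **That leaving out recruitment cohort is a second design mismatch.** Cohort is not named as a stratification factor. The second cohort's diaries fall "in 2007 and 2008 (second cohort"), a year later than the first cohort's, but nothing says that mite exposure differed between those autumns. Cohort is also an imperfect marker of season: under Outcome measures, patients with too few second-year diary days contribute first-year data, so autumn 2007 can appear in both cohorts.
- **That the primary test is invalid.** The error runs towards caution and produces no bias.

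**Conclusion.** The point holds in a narrow form. The sole documented stratification factor is absent from a closed covariate list, and the baseline score that might replace it is not identified. If that score is not the stratification variable and telephone severity has prognostic value beyond it, the standard error is overstated by up to about 5%; otherwise it is essentially correct. These sizes rest on assumed correlations, two assumed strata and assumed block sizes, none of which the article gives. The loss is small, would not change a decision at the planned effect size and leaves the sample size as it is. The case for acting is that the correction is nearly free and makes the analysis match the randomisation.

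**What to change.** Add the severity stratum, coded as in the randomisation list, as a fixed factor in the primary ANCOVA and in the matching models for the secondary outcomes. State which recorded measurement is the baseline nasal sum score. Recruitment cohort may be added as an optional covariate for precision, not as a design term.

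The cost is two sentences and (number of strata − 1) degrees of freedom. With two strata (assumed) and 192 evaluable patients, the residual degrees of freedom go from 192 − 5 = 187 to 186. The article describes the trial as ongoing, with second-cohort diaries running through autumn 2008, so as of the article the change could be specified before unblinding.

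### Minor: the random family effect should be in the primary model whenever siblings contribute, not only when a pre-test at P < 0.20 is positive

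*Protocol article*

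**What the plan says.** The Data analysis section of the protocol article fixes the primary comparison: the "mean daily sum score from the diary after two years will be done using Analysis of Covariance", adjusted for "baseline nasal sum score at entry into study, age of patients, and presence of cat allergy". It then foresees siblings: "In case more than one child from the same family has been included in the study and contribute to the final analysis", the plan is that "we will test whether 'family' provides a statistically significant effect (P < 0.20"). The consequence follows: "In that case 'family' will be added as a random effect". If the test is negative, siblings enter the ANCOVA as independent children.

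Nothing else in the article deals with siblings. The Randomization section describes stratification by severity only. The Sample size calculation section makes no allowance for family clustering. The number of sibling families, the expected correlation and the type of test for family are not given.

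**The concern.** Whether siblings are independent is a matter of design, and a significance test on the trial data does not settle it. Siblings usually share a home. The article itself treats the home as relevant, since dust from the child's bedroom floor and mattress is sampled to measure mite exposure. A non-significant result from a handful of pairs is weak evidence of independence, yet under this rule it decides that siblings are treated as independent.

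Two things are at stake. The standard error of the treatment effect may not match the sibling structure: too small if ignored pairs mostly share an arm, too large if they are mostly split. And the primary confidence interval and p-value come from whichever of two models the outcome data select. Because the article states the rule outright, this is a choice already made, and not a detail left to an unseen analysis plan.

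**Working it through.** **The plan's own figures.** The article gives no figure for clustering. Its sample sizes reproduce for independent children. With a standardised difference of 0.5 ("A 30% change would provide a delta of approximately 0.5"), two-sided 5% and the stated 95% read as power, a t-based calculation gives 105 per group; 96/0.75 = 128. Neither depends on the family rule.

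**Inputs.** From the article: 251 randomised and 25% expected dropout, so 251 × 0.75 ≈ 188 evaluable; no family-based allocation described. Assumed, because the article is silent: 5 to 30 sibling pairs and a residual intra-family correlation ρ of 0 to 0.5.

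**Step 1: how often the pre-test misses real clustering.** Take a one-way ANOVA on m pairs. The test is positive if F exceeds the upper 20% point of F(m−1, m). Under correlation ρ, F is distributed as (1+ρ)/(1−ρ) times that central F.

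| Pairs | ρ | Critical value | (1+ρ)/(1−ρ) | Power | Missed |
|---|---|---|---|---|---|
| 10 | 0.3 | 1.741 | 1.857 | 0.534 | 47% |
| 20 | 0.3 | 1.470 | 1.857 | 0.693 | 31% |
| 20 | 0.5 | 1.470 | 3.000 | 0.937 | 6% |
| 30 | 0.5 | 1.366 | 3.000 | 0.981 | 2% |

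As a cross-check, a REML likelihood-ratio test was simulated with 190 analysed, treatment plus three covariates, and 3,000 runs per scenario. Two reference distributions were used: the 50:50 mixture and the plain chi-square. At ρ = 0.3 the miss rate is 44% or 60% with 10 pairs and 31% or 47% with 20 pairs (mixture or plain). At ρ = 0.5 it is 6% or 12% with 20 pairs and 2% or 5% with 30. The unnamed choice of test therefore moves the answer.

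**Step 2: what a miss does to the standard error.** With equal arms, C pairs in the same arm and D pairs split,

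true variance / naive variance = 1 + 2ρ(C − D)/188.

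- Extremes, 20 pairs, ρ = 0.3: 1 ± 0.3 × 40/188 = 0.936 to 1.064, so the standard-error ratio is 0.968 to 1.031.
- Extremes, 20 pairs, ρ = 0.5: 0.894 to 1.106, so 0.945 to 1.052.
- Typical case: under individual randomisation each pair shares an arm with probability about 1/2. C − D then has mean about 0 and SD √20 ≈ 4.47. One SD at ρ = 0.3 gives 2 × 0.3 × 4.47/188 = 1.4% in variance, or 0.7% in standard error; 1.96 SD gives 1.4%. At ρ = 0.5, one SD gives 1.2%.

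**Step 3: effect on the treatment test.** The same simulation, with individual randomisation over 5 to 30 pairs and ρ from 0 to 0.5, gives these two-sided type I error rates (Monte Carlo standard error about 0.4 points):

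| Model | Type I error |
|---|---|
| Pre-test, then the selected model | 4.4% to 6.0% |
| Family always included | 4.4% to 5.9% |
| Family always ignored | 4.2% to 5.6% |

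With ρ = 0.3 and sibling allocation forced, ignoring family gives 5.1% to 6.0% if all pairs share an arm and 4.4% to 4.7% if all are split.

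**Step 4: precision.** The variance of the generalised least-squares estimate relative to ordinary least squares, at known ρ = 0.3, 188 children and random allocation, averages 0.990, 0.980 and 0.970 for 10, 20 and 30 pairs. That is a gain of 1% to 3%, and somewhat less once ρ has to be estimated.

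**The case against.** The best defence is that the rule is harmless. It is written in advance, has two outcomes, leaves the covariates and treatment term alone, and uses a liberal threshold that leans towards inclusion. The authors saw the clustering and planned for it. Adjustment for baseline score, age and cat allergy may absorb part of what siblings share. Misses are concentrated where clustering is too weak to matter. All of this stands, and it sets the priority.

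Three stronger readings are tempting and should not be drawn:

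- **That the pre-test inflates the false-positive rate.** Step 3 shows no material inflation. If anything, always including family runs marginally higher than ignoring it in most scenarios, by at most 0.9 points.
- **That the test's roughly 20% positive rate without clustering is a fault.** A positive test only adds the random effect, and the remedy adds it every time.
- **That the test has low power where clustering is strong.** With 20 to 30 pairs and ρ = 0.5, the ANOVA test detects it in 94% to 98% of trials.

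What the defence does not supply is a benefit from the pre-test. It makes the primary model depend on the outcome data and on an unspecified test, and it gives up a little precision when it misses.

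**Conclusion.** The point holds as a minor improvement. The stated rule can drop a foreseeable correlation from the primary model because of a non-significant test. How often depends on figures the article does not give: about a third to a half of trials for 10 to 20 pairs at ρ = 0.3, and rarely with many strongly correlated pairs. The damage is small in either case. At ρ = 0.3 the typical standard-error discrepancy is under 1%, with no preferred direction.

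A reader might take the 3% to 5% extremes as the expected error. The article does not support that: it describes no allocation by family, so having every pair concordant or every pair split is very unlikely. Nor does the rule leave room for discretion after the data are seen; the model is selected by data, but under a pre-stated rule. The sample size and the validity of the trial are not in question.

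**What to change.** Delete the pre-test. State that, when more than one child from a family contributes, the primary ANCOVA always includes a random intercept for family, with single children as families of one. Family-clustered robust standard errors are an alternative. Because the pairs may be few, name a small-sample degrees-of-freedom method (for example Kenward–Roger), and say that a family variance estimated at zero returns the ordinary ANCOVA.

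The cost is one sentence, to be settled before unblinding. Recruitment, data collection and sample size are unchanged. The trial report should also give the number of sibling families and how many share an arm, so that readers can see how little or how much depends on this.
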